## Abstract

**Background:**

The proportion of 60+ years with excessive alcohol intake varies in western countries between 6–16 % among men and 2–7 % among women. Specific events related to aging (e.g. loss of job, physical and mental capacity, or spouse) may contribute to onset or continuation of alcohol use disorders (AUD). We present the rationale and design of a multisite, multinational AUD treatment study for subjects aged 60+ years.

**Methods/Design:**

1,000 subjects seeking treatment for AUD according to DSM-5 in outpatient clinics in Denmark, Germany, and New Mexico (USA) are invited to participate in a RCT. Participants are randomly assigned to four sessions of Motivational Enhancement Treatment (MET) or to MET plus an add-on with eight sessions based on the Community Reinforcement Approach (CRA), which include a new module targeting specific problems of older adults. A series of assessment instruments is applied, including the Form-90, Alcohol Dependence Scale, Penn Alcohol Craving Scale, Brief Symptom Inventory and WHO Quality of Life. Enrolment will be completed by April 2016 and data collection by April 2017.

The primary outcome is the proportion in each group who are abstinent or have a controlled use of alcohol six months after treatment initiation. Controlled use is defined as maximum blood alcohol content not exceeding 0.05 % during the last month. Total abstinence is a secondary outcome, together with quality of life andcompliance with treatment.

**Discussion:**

The study will provide new knowledge about brief treatment of AUD for older subjects. As the treatment is manualized and applied in routine treatment facilities, barriers for implementation in the health care system are relatively low. Finally, as the study is being conducted in three different countries it will also provide significant insight into the possible interaction of service system differences and related patient characteristics in predictionof treatment outcome.

**Trial registration:**

Clinical Trials.gov NCT02084173, March 7, 2014.

## Introduction

For several decades the prevention of adolescent high-risk alcohol use and the treatment of middle aged patients with alcohol use disorders (AUD) have been major public health targets. Less attention has been paid to the development of AUD treatment programs that are tailored to specific treatment needs of older adults (60+ years) with AUD. We report on the rationale and design of a multi-centre treatment study conducted in Denmark, Germany and USA for this age group.

## Background

### Prevalence

The proportion of older adults with problematic alcohol consumption is of considerable size. In Denmark the share of men aged 65 years and older drinking more than the official Danish “high-risk” limit of 21 standard drinks (1 standard drink = 12 g pure alcohol) per week has declined from 13.8 % in 2010 to 11.7 % in 2013, with a similar decline for women drinking above the “high-risk” limit of 14 standard drinks per week from 8.2 % to 6.9 % [1]. However, proportions are high, and because of the increasing number of people reaching a higher age the absolute number is also increasing. In Germany the percentage of men aged 60–64 years drinking at hazardous level or above (>60 g pure alcohol per day) has been reported to be 6.2 % and among women in the same age group the percentage was 1.6 % (>40 g pure alcohol per day) [2]. Among older adults in residential care facilities 14 % have a misuse of alcohol [3], and among patients aged 75 years and older in general practice 6.5 % have at-risk alcohol consumption [4]. In the USA among persons aged 65 and older 16 % of men and 4 % of women reported an unhealthy drinking pattern (monthly use exceeding 30 drinks or heavy episodic drinking of four or more drinks in any single day during a typical month in the previous year) [5]. In the National Survey on Drug Use and Health 6.7 % of 65 years and older persons reported alcohol abuse or alcohol dependence according to DSM-IV, and among past-year alcohol users the proportion was 15.4 % [6]. In this age group 13 % of men and 8 % of women showed at-risk drinking, and 14 % of men and 3 % of women binge drinking [7].

### Age-related risk- factors and drinking motives

Older adults with a high level of alcohol consumption constitute a heterogeneous group with different histories of alcohol consumption. Some have started drinking excessively early in life and have survived into late adulthood continuing their level of alcohol consumption or experiencing periods of recovery and exacerbation; some have started drinking excessively during middle life, continuing their alcohol consumption which may become more problematic with increasing age; and some have started drinking excessively late in life. To our knowledge there are no data on the distribution of these different groups within older adults. Different causes for late-onset drinking have been put forward: difficulty in coping with loneliness, deteriorating social function, retirement, depression, sadness, bereavement, hopelessness, and others [8, 9]. Some may cope with losses and loneliness by drinking [10].

### Age-related negative alcohol use consequences

Light alcohol consumption has consistently been reported to have a protective effect on cardiovascular illness as well as on mortality, including all-cause mortality [11–13]. Alcohol may improve self-esteem, provide relaxation, and is often, but certainly not always, consumed socially [14]. However, AUD-related negative consequences clearly outweigh these beneficial effects, and the threshold for harmful effects becomes lower as age increases. The psychosocial consequences of AUD among the older adults may not be as severe as in younger subjects, as average severity of AUD is generally lower compared to younger persons, and therefore behaviour is less affected by the alcohol consumption [4, 15]. Excessive alcohol intake in the older adults may increase the risk of a number of conditions and diseases, including hypertension [16, 17], hemorrhagic stroke [12], diabetes mellitus [18], alcoholic liver disease and other diseases in the gastrointestinal system, including gastritis and ulcers with increased risk of bleeding, infectious diseases [19], pulmonary diseases [20], and falls with fractures as a consequence [21]. There is clear evidence that in a dose-dependent pattern alcohol increases the risk of cancer in many organs, including oropharynx, larynx, oesophagus, liver, colon-rectum, and breast [22]. In addition, older adults may have physical and mental co-morbidities that are treated with various medications, introducing risk of harmful interactions between alcohol and medication [23]. Further on, current data suggests that AUD is associated with an increased risk of depression, [24]. Suicide is closely linked to depression and alcohol use. AUD may predispose to suicidal behaviour through the increased risk of depression and promotion of adverse life events [25]. Excessive alcohol intake may be associated with increased risk of cognitive decline and dementia [26], although data are conflicting.

Other studies on treatment of AUD have included older adults, but the treatments have not been targeting the older adults and rarely data specifically on this age group are reported. As the western societies age rapidly in the coming years older adults may be an increasing challenge to treat. Given this background, we conduct a randomized controlled clinical trial for subjects aged 60+ with DSM-5 AUD, with one standard and one age-adapted brief intervention.

### Objectives

As an overall aim we strive to provide better treatment for older people with AUD. As first objective we will examine the effects of standard Motivational Enhancement Therapy (MET), a very brief treatment based on motivational interviewing. A Cochrane Review concluded that MET was clearly more effective than no treatment [27]. Since older individuals with AUD tend to be psychosocially less affected by alcohol use, brief treatment is seen at least as appropriate as it is for younger persons with alcohol problems [28]. Second, in order to specifically address the needs of older adults, we will examine whether an add-on to standard MET will produce greater improvement compared to MET alone. This add-on is The Community Reinforcement Approach (CRA) [29]. The CRA approach is based on the belief that the surrounding environment can play a powerful role in encouraging or discouraging alcohol use. Consequently, it utilizes social, recreational, familial, and vocational reinforcers to assist people in the recovery process. The underlying perspective of CRA is relatively simple: In order for a person to give up a significant reinforcer such as alcohol use, the alternative needs to be more rewarding. Because old age is a period of transitions with risk of or certainty of losses, for example retirement and loss of friends and family members, we have developed an additional module in CRA targeting the specific needs older adults may encounter. Whether or not drinking is a problem, the loss of sources of positive reinforcement may be a significant life transition as people age, and a significant decrease in positive reinforcement is a common precipitant of problem drinking [30]. Thirdly, we analyse possible culture-related differences of alcohol-related care, patient characteristics and treatment outcome in the three States participating, Denmark, Germany, and the USA. To our knowledge, this is the first study of its kind: A study specifically targeting the treatment of older adults (60+ years) with alcohol problems and including 3 countries across the Atlantic Ocean.

## Methods

### Design and settings

The study is conducted as a multicentre, multinational single-blind randomized controlled study, with outpatient alcohol treatment facilities in Denmark (3 sites), Germany (10 sites), and USA (New Mexico) (1 site). We started in spring 2014 and enrolment is expected to finish by April 2016. So far (August 2015) nearly 550 participants have been enrolled.

In Denmark the municipalities offer alcohol treatment in outpatient facilities. Treatment is free and is given to all persons contacting the outpatient clinics. Patients can be treated without a referral but can approach the clinics directly. In Germany treatment is offered by a specialized addiction care system. Counseling and treatment is free: the facilities receive city and State funds for outpatient services. In New Mexico and Germany patients over 60 years do not frequently seek treatment for addiction in specialty care settings. However, in New Mexico, they often see primary care providers, making primary care settings particularly promising for the detection and treatment of substance use disorders in older people in the USA. Therefore, in Albuquerque the study is implemented in a primary care clinic. In Germany, in addition to outpatient counselling centers that belong to the addiction care system, treatment is offered at the research institution (Technische Universitaet Dresden) or an outpatient psychotherapy clinic (Munich). In all three countries staff education is high and specialized training is mandatory. Finally, in all three countries, detoxification, if necessary, is offered before treatment.

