### Statistical analyses

Multiple logistic regression models will be used to analyse primary and secondary outcomes, and explanatory variables will include treatment, site, gender and age as well as other relevant demographic variables. The statistical analyses will be based on an “intent-to-treat”-approach, thus all patients randomized to treatment will be included. A multiple imputation strategy will be used in case of missing explanatory variables. The primary hypothesis of differences between treatment conditions will be tested one-sided since MET + CRA treatment is an extension of MET treatment. All other hypotheses will also be tested one-sided. In addition, we will perform a participation analysis where a logistic regression analysis is used to investigate how available demographics characteristics affect the probability that an individual will accept participation in the study.

The primary outcome is abstinence *or* controlled use as stated above. Information from the Form-90 is used to calculate the BAC based on the Widmark formula with an age adjustment [43].

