### Quality assurance and fidelity monitoring

Several procedures are employed to ensure and document fidelity of the two study treatments.

*All therapists are trained in both treatments*. The therapists are assigned before randomisation and must therefore be able to deliver both. As 3 different countries and 16 sites participate, the training program has two steps: First, a minimum of 2 therapists from each sites participated in a “train-the-trainers” – conference in Denmark. At this 5-day conference the therapists were introduced to the therapies and trained extensively. These trained therapists subsequently train all other participating therapists locally at each site. Therapy sessions are digitally audio-recorded. Local supervisors at each site, experienced in the treatment and in supervision, continuously review randomly drawn sessions from each therapist and give feedback to therapists to ensure concordance with the treatment manuals. On-going supervision includes biweekly Skype meetings between all local supervisors and the overall supervisors on the treatment delivery in order to discuss and synchronize treatment delivery across sites, and secure treatment manual adherence.

*Treatment fidelity monitoring* is based on digital recordings of all sessions performed in the study. A random sample equivalent to 10 % of all sessions is drawn and scored by independent coders using the methodology of MITI 4 (Motivational Interviewing Treatment Integrity) [44] to measure fidelity to the style of the therapy. In addition, the coders complete a checklist of the content in the sessions.

*Data collection* is performed by research assistants (interviewers) not involved in the treatment and blinded to treatment assignment. Data collection is based on manualized procedures, and data are directly entered into the database through iPads or computers. The data forms are programmed with logical rules and allowed values, thus assisting the interviewer during the process. Data quality and completeness is continuously monitored. Twenty percent of the air samples are randomly selected for analysis to validate the self-reported data.

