### Innovative aspects

The present study will gain new insights into older adults seeking treatment for their alcohol misuse. This has only been the focus of a small number of studies so far. Not only will new data be available, but simultaneously from different countries and cultures across the Atlantic Ocean. This will add to the generalizability of the results or provide information about the cross-cultural differences in treatment effects. If the treatment offered is successful the study will also show that a brief intervention is feasible and is easy to implement for this age group. In addition, as the design is an add-on design, the study will gain information about whether a very brief intervention focusing on motivation and planning for change is sufficient or including modules dedicated to help the patient execute these changes achieve better outcomes. In addition, information on patient characteristics that predict better results in both treatment conditions will help to improve assignment of brief interventions to elderly subjects with AUD. Further, as a module in the adapted CRA is dedicated to the needs of older adults this will provide knowledge about whether such a target is relevant or not. Finally, the study will provide data on the use of hair samples when assessing alcohol use.

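### Country differences are presented as cultural, but the USA is one primary-care site, so country, site and setting cannot be separated there; the blanket one-sided rule also does not fit these comparisons

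*Protocol article*

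**What the plan says.** The third aim under Objectives reads: "Thirdly, we analyse possible culture-related differences of alcohol-related care, patient characteristics and treatment outcome in the three States participating". In the Discussion, Innovative aspects says the multinational data will either add to generalizability or "provide information about the cross-cultural differences in treatment effects".

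Design and settings lists three Danish sites, ten German sites and one US site. Danish treatment is given in municipal outpatient alcohol facilities. German treatment is given in addiction counselling centres and, in addition, at a research institution or a psychotherapy clinic. For the USA, "in Albuquerque the study is implemented in a primary care clinic", because older people in New Mexico often see primary care providers but seldom seek specialty addiction care. No primary-care site is named for Denmark or Germany.

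Statistical analyses describes multiple logistic regression for the primary and secondary outcomes, in which "explanatory variables will include treatment, site, gender and age as well as other relevant demographic variables". The same section states that the primary hypothesis, and then all other hypotheses, will be tested one-sided. The reason given for the primary hypothesis is that MET + CRA extends MET.

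**The concern.** Two things do not fit together.

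First, a US difference from the other countries may reflect culture, the primary-care route into treatment, or that one clinic and its staff. The setting was chosen because of where older New Mexico patients seek care, so even the descriptive comparison of patient characteristics mixes culture with recruitment route. Calling such a difference cultural claims more than the design can show.

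Second, the one-sided rule covers all other hypotheses without exception. Its rationale concerns adding CRA to MET and does not extend to countries. No direction is stated for any country difference, and a joint comparison of three countries has no natural one-sided form. If a direction were chosen after seeing the data, the true type I error of a nominal 5 % one-sided test would be 10 %.

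At stake is what the trial may conclude about countries, both in outcome level and in the effect of adding CRA.

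**Working it through.** **The plan's own figure.** Power calculation gives 50 % versus 60 %, one-sided 5 %, 90 % power. With pooled variance and no continuity correction:

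n = [1.645 × √(2 × 0.55 × 0.45) + 1.282 × √(0.50 × 0.50 + 0.60 × 0.40)]² / 0.10² = (1.157 + 0.897)² / 0.01 ≈ 422.0, rounded up to 423 per arm.

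423 / 0.85 = 497.6, rounded up to 498 and in the plan to 500. The stated figures reproduce. They cover the overall two-arm comparison only.

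**What the named variables can estimate.** Take the 3 + 10 + 1 = 14 sites in Design and settings.

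- 14 site indicators plus treatment: rank 15.
- Adding country main effects: rank still 15, because each country is a sum of its site indicators. Country differences in outcome level remain available as contrasts of site coefficients.
- Adding treatment-by-country terms: rank 17. Two further parameters are estimable, but they are not among the variables named.
- The US country indicator is identical to the US site indicator, and the primary-care indicator is the same column again.

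Without an interaction the model has one treatment odds ratio for all countries. Country-specific risk differences derived from it would vary only because outcome levels and covariates vary.

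**Precision of a difference in treatment effect.** Inputs: 500 per arm and 15 % dropout, so 425 evaluable per arm; rates 0.50 and 0.60, so the variance sum is 0.25 + 0.24 = 0.49. Assumptions: the US total (no split by country is given) and 1:1 allocation within the USA.

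SE of the US risk difference = √(0.49 / n_US). SE of the US-minus-rest difference = √(0.49 / n_US + 0.49 / n_rest), with n per arm. Detectable difference at 80 % power, two-sided 5 % = (1.960 + 0.842) × SE = 2.80 × SE.

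| Assumed US total | n_US per arm | n_rest per arm | 95 % half-width, US risk difference | SE of difference in effects | Detectable difference | Power for 10 points |
|---|---|---|---|---|---|---|
| 100 | 42.5 | 382.5 | 21 points | 0.113 | 32 points | 14 % |
| 150 | 63.75 | 361.25 | 17 points | 0.095 | 27 points | 18 % |
| 300 | 127.5 | 297.5 | 12 points | 0.074 | 21 points | 27 % |

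For 150: √(0.49/63.75 + 0.49/361.25) = √(0.00769 + 0.00136) = 0.0951, and 2.80 × 0.0951 = 0.266.

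**Precision of a difference in outcome level.** With one US site, site-to-site variation within the USA cannot be estimated. As an illustration, if success rates vary between sites with an SD of 5 to 10 points (an assumption), that variation alone adds an SE of SD × √(1/1 + 1/10), or 5.2 to 10.5 points, to a USA-versus-Germany contrast, however many patients are enrolled.

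**The case against.** The strongest reply has four parts.

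- **The model list is open.** The text says what the variables will include and never says main effects only. A reader might infer that the plan has fixed a main-effects model and that the missing interaction is itself an error. The article does not support that: a condensed protocol may leave such a term to the full protocol or SAP. What stands is narrower: the variables named do not by themselves yield differences in treatment effect.
- **The third objective is wider than treatment effects.** It names care, patient characteristics and outcome. The first two need no outcome model, and outcome level by country can be read from site contrasts. A reader might infer that the whole objective is unanswerable; that goes too far. The limit is on attributing a US difference to culture.
- **Settings are disclosed.** Design and settings explains the US choice, Challenges mentions differing treatment cultures and health-care organisation, and the Abstract already speaks of "significant insight into the possible interaction of service system differences and related patient characteristics". This is fair, and the Abstract needs little change. But Objectives and Innovative aspects still use the cultural label without that qualification.
- **No country hypothesis is listed.** A priori hypotheses contains two, neither about country, so the one-sided rule may never have been meant for country comparisons. That is possible, but the rule as written has no exception.

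A reader might also fault the sentence in Innovative aspects on "information on patient characteristics that predict better results in both treatment conditions", since purely prognostic factors cannot choose between arms. The sentence goes on to speak of assigning brief interventions to older patients, and can be read as asking who suits brief treatment at all. It is loosely worded, not shown to be wrong.

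**Conclusion.** The point holds in a limited form. A US difference cannot be attributed to culture, because country, site and primary-care setting coincide there; this follows from the design and no analysis can undo it. Denmark and Germany have several sites each, so neither is aliased with a single site. The one-sided rule does not fit undirected country comparisons.

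Any statement about differing treatment effects would be imprecise: detectable differences of roughly 32 to 21 points for an assumed 100 to 300 US patients, two to three times the planned 10. That range rests on the assumed US share, the planned response rates and 15 % dropout.

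A reader might infer that the main result is compromised. It is not: the randomised comparison with site in the model does not depend on separating country from setting, and 423 per arm is correct.

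As a side point, Design and settings sums to 14 sites, while Quality assurance and fidelity monitoring says "As 3 different countries and 16 sites participate".

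**What to change.** 1. In Statistical analyses, exempt country comparisons from the one-sided rule and test them two-sided.
2. If the statement on differing treatment effects in Innovative aspects is kept, base it on a treatment-by-country interaction, reported with country-specific risk differences and 95 % CIs. Otherwise remove the statement.
3. In Objectives and Innovative aspects, call these results exploratory country and service-setting differences, and say that for the USA the two cannot be separated.
4. Reconcile the site counts of 14 and 16, since site is a model covariate.

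The cost is a few sentences and, if the effect statement is kept, two model terms. The plan must accept that these comparisons are imprecise. Sample size and primary analysis stay as they are.
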